4.4 Exclusion Criteria for STEP II

If a subject meets any of the following exclusion criteria, they should not receive Dose #2 (see section 6.4).

- 4.41 Has received a non-licensed agent (vaccine, drug, biologic, device, blood product, or medication), other than from participation in this study, since Dose #1, or expects to receive another non-licensed agent before the end of the study.
- 4.42 Use of anti-cancer chemotherapy or radiation therapy since Dose #1, new diagnosis of an active malignancy, or is immunosuppressed as a result of an underlying illness (other than HIV-1 infection) or treatment.
- 4.43 Use of glucocorticoids, including oral or parenteral steroids ( $\geq 2$  mg/kg per day or  $\geq 20$  mg total dose) for more than 2 weeks since vaccine Dose #1, or high-dose inhaled steroids ( $>800$  mcg/day of beclomethasone dipropionate or equivalent) since Dose #1 (nasal and topical steroids are allowed).
- 4.44 Has received immunoglobulin or other blood products since Dose #1.
- 4.45 Any Grade 3 toxicity or adverse event experienced by a subject unless the investigator has received protocol team approval.

- 4.46 Any Grade 4 toxicity or adverse event (other than injection site reaction or fever) that is definitely, probably or possibly related to study vaccine.
- 4.47 Any Grade 4 injection site reactions or fever experienced by a subject, unless the investigator has received protocol team approval.
- 4.48 Any Grade 4 adverse events that are definitely not or probably not related to study vaccine, unless the investigator has received protocol team approval.
- 4.49 New occurrence or new awareness of Guillain-Barré Syndrome in the subject or subject's family (parents, siblings, half siblings, or children) since Dose #1.
- 4.410 A new onset of a neurological disorder including (but not limited to) absent ankle and patellar deep tendon reflexes in both legs (all four absent) since Dose #1.
- 4.411 Disproportionate loss of strength in lower extremity or extremities, compared to the upper extremities (not thought to be related to pregnancy) since Dose #1.
- 4.412 Documented **2009 H1N1 Influenza A infection** since Dose #1 (see 4.23 for definition)
- 4.413 The subject, parent, or guardian refuses further vaccination.
- 4.414 Any new disease which the investigator judges to be clinically significant or clinically significant findings since Dose #1 that, in the investigator's opinion, would compromise the safety of the subject.

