### 5.3 Dose Modifications

There will be no dose modifications. Subjects who do not receive the Dose #2 will be asked to return for safety assessments and for scheduled blood sample collections for immunogenicity assessments (see section 6.4).

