**For this protocol, the following definition of H1N1 infection will be used:**  
**“Symptoms of influenza-like illness as well as a proven history, by RT-PCR, of novel influenza H1N1 infection, or, has positive influenza diagnostic testing since June 2009 (specificity to H1N1 not required) prior to study entry.”**

**If a subject experiences documented H1N1 infection, as defined in Section 4.23, between Step I and Step II of the protocol, the subject should NOT receive the second dose of vaccine but should continue to be seen at the scheduled study visits, and have blood collected, as per the Schedule of Evaluations.**

Antipyretics should not be routinely given in anticipation of adverse events after vaccination, but should not be withheld if symptoms occur. Antipyretics should be recorded when given.

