6.4. Criteria for Permanent Exclusion from Second Dose of Vaccine

If a subject meets any of the exclusion criteria described in section 4.4, Dose #2 cannot be administered. If a subject is excluded from receiving Dose #2 of **Influenza A (H1N1) 2009 monovalent vaccine**, site staff should make all reasonable attempts to request the subject return to clinic for the 7 month visit (end of study). Every attempt should be made to maintain phone contact, to monitor for safety, throughout the study period.

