## 8.2 Endpoints and Outcome Measures

### 8.21 Primary Endpoints:

#### 8.211 Adverse Events of Grade 3 or higher severity, including:

- Abnormal laboratory values, signs and symptoms or diagnoses.
- Solicited local AEs, including pain, tenderness, redness, and swelling post each vaccination.
- Solicited systemic AEs, including feverishness, malaise, body aches (exclusive of the injection site), nausea, and headache post each vaccination.

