7. Reactogenicity assessments will briefly review the subject's history and provide an assessment of AEs at 30 minutes post vaccination and at all telephone calls. Assessments will include review of:
  - erythema,
  - induration,
  - pain and tenderness at the injection site,
  - fever,
  - fatigue,
  - myalgia (exclusive of the injection site),The following clinical evaluations will also be collected by interviewing the subject:
  - Assessment of eligibility prior to Dose #1 and Dose #2
  - All unplanned health care provider visits will be reported on the appropriate CRF.
8. Chemistries (SGOT, SGPT and creatinine ONLY) should be obtained within 30 days prior to administration of Dose #1 to obtain a baseline record. The same chemistries should be repeated at the STEP II Day 10 visit, to determine any liver or renal toxicity related to study vaccine.
9. CBC within 30 days; chart abstraction may be used
10. Immunophenotyping, including CD4, CD8, and CD19, within 30 days prior to study entry. Testing obtained for clinical care may be used if available. If not available, study specific immunophenotyping should be obtained. It may be run in the CLIA certified laboratory, at the clinical site. It does not need to be run at a DAIDS IQA certified laboratory.

11. HIV-1 RNA obtained from medical record within 30 days of study entry. It may be run in the CLIA certified laboratory, at the clinical site. It does not need to be run at a DAIDS VQA certified laboratory.
12. Blood draw volumes for PBMC/plasma for the various age groups should be no more than the following:  
     $\geq 4$  to  $< 6$  years of age: 11.0ml  
     $\geq 6$  to  $< 25$  years of age: 20.0ml
13. Directions for collection, processing, storage and shipping can be found in the P1088 Manual of Operations (MOP) and the Laboratory Processing Chart (LPC).
14. HAI will be performed for **H1N1 2009 H1N1 Influenza A virus** at all visits and for influenza viruses contained in the 2009-2010 vaccine preparation at the screening and 7 month visits.

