15. Respiratory specimens, including nasopharyngeal swab, nasal wash, or tracheal aspirate obtained at an unscheduled sick visit for evaluation of influenza like illness (ILI). Instructions for nasopharyngeal swab collection can be found in the MOP. All respiratory specimens will be processed, stored frozen and batched shipped to University of Colorado laboratory as per P1088 MOP and LPC. Respiratory specimens are not required for unscheduled sick visits if the subject is being assessed for possible AEs or GBS, without ILI.
16. STEP I Day 21 and STEP II Day 0 (Dose #2) visits should occur on the same day. However, if a subject comes in to clinic for Dose #2 and is found to have a reason for deferment of STEP II entry, such as fever, Dose #2 may be deferred for up to 7 days (28 days post Dose #1). Day 21 study evaluations should be completed. If the reason for deferral is ILI, a respiratory specimen should be collected. If Dose #2 is delayed beyond 72 hours, a history, physical, neurologic examination, pregnancy test should be repeated prior to administration of Dose #2.
17. If a female subject has a positive urine or serum pregnancy test (hCG) on STEP I Day 21, enrollment in STEP II should NOT be performed and Dose #2 vaccination should NOT be administered until  $\geq 14$  weeks of gestation. (See SOE, Appendix IB.)
18. Unscheduled visits are for assessment of ILI, possible Guillain-Barre syndrome or possible AEs. Subjects should be asked to return to clinic within 24 hours of development of symptoms consistent with Guillain-Barre syndrome; within 72 hours for assessment of possible adverse events other than GBS or for symptoms consistent with ILI.
19. For subjects who choose to prematurely discontinue the study, the early study discontinuation visit should occur.

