8. Chemistries (SGOT, SGPT and creatinine ONLY) should be obtained prior to administration of Dose #2. The same chemistries should be repeated at Day 10 post Dose #2 to determine any liver or renal toxicity related to study vaccine.
9. CBC within 30 days; chart abstraction may be used
10. Directions for collection, processing, storage and shipping can be found in the P1088 Manual of Operation (MOP)
11. A targeted medical history includes birth and neonatal history including
  - Congenital anomalies
  - List of all medications taken since birth
12. Physical exam should include height, weight, vital signs (temperature, heart rate, and respirations).
13. Neonatal neurological exam
14. Unscheduled visits are for assessment of ILI, possible Guillain-Barre syndrome (GBS) and possible AEs. Subjects should be asked to return to clinic within 24 hours of development of symptoms consistent with GBS; and within 72 hours for assessment of possible adverse events (other than GBS) and for symptoms consistent with influenza-like illness (ILI).
15. Subjects who prematurely discontinue study prior to delivery of their infant require the early treatment discontinuation visit.

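### Subjects permanently excluded from Dose #2 have no scheduled liver or renal test after vaccination, because the only post-vaccine chemistries sit at a visit dated from Dose #2

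*Combined protocol and SAP*

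**What the plan says.** Appendix IA, footnote 8, limits the chemistries to SGOT, SGPT and creatinine. The baseline is taken within 30 days before Dose #1. The follow-up is set by one sentence: "The same chemistries should be repeated at the STEP II Day 10 visit, to determine any liver or renal toxicity related to study vaccine". The column heading places STEP II Day 10 at 7 to 13 days after the second dose.

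For subjects who never receive Dose #2:

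- Section 6.4 says "site staff should make all reasonable attempts to request the subject return to clinic for the 7 month visit (end of study" and adds telephone contact for safety.
- Section 5.3 says they "will be asked to return for safety assessments and for scheduled blood sample collections for immunogenicity assessments (see section 6.4".
- Sections 6.2 and 6.5 say that a subject with H1N1 infection between the steps "should continue to be seen at the scheduled study visits, and have blood collected, as per the Schedule of Evaluations".
- Appendix IA, footnote 19, covers those who leave: "For subjects who choose to prematurely discontinue the study, the early study discontinuation visit should occur".

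The grounds for exclusion in section 4.4 include "Any Grade 4 toxicity or adverse event (other than injection site reaction or fever) that is definitely, probably or possibly related to study vaccine" (4.46). They also include steroids (4.43), blood products (4.44) and refusal of further vaccination (4.413).

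The primary safety endpoint of Grade 3 or higher events (8.211) opens with "Abnormal laboratory values, signs and symptoms or diagnoses".

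**The concern.** The protocol sets one laboratory check for liver and kidney toxicity and ties it to a visit that exists only if Dose #2 is given. Subjects excluded from Dose #2 have been vaccinated, yet the schedule gives them no such check. Some of them are excluded because they reacted to Dose #1, and withholding Dose #2 for that reason is itself a primary endpoint (8.213). The missing test is therefore not random with respect to tolerance.

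Two things are at stake. One is individual safety: a rise in SGPT or creatinine without symptoms prompts no visit and would go unseen. The other is ascertainment. Section 8.611 gives no rule for a vaccinated subject with no post-vaccine chemistry, so such a subject could be counted as free of laboratory events without having been tested.

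**Working it through.** **Step 1. Is the gap real, or an artefact of a broken table?** The Appendix IA blood rows can be summed by visit and compared with the printed totals (mL).

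| Visit | Tubes listed | Sum | Printed total | Chemistry tube |
|---|---|---|---|---|
| Screening (before vaccine) | chemistries 2 + CBC 1 + immunophenotyping 2 + HIV-1 RNA 2 + PBMC 11-20 + HAI 2 | 20-29 | 20-29 | yes |
| STEP I Day 21 | CBC 1 + PBMC 11-20 + HAI 2 | 14-23 | 14-23 | no |
| STEP II Day 10 | chemistries 2 + PBMC 11-20 + HAI 2 | 15-24 | 15-24 | yes |
| 7 months | HAI 2 | 2 | 2 | no |
| Unscheduled | none | - | none | no |
| Early discontinuation | PBMC 11-20 + HAI 2 | 13-22 | 13-22 | no |

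Every printed total is reproduced. Only screening and STEP II Day 10 need the 2 mL chemistry tube to reach their totals, so the table has not lost an entry.

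**Step 2. Does any other text supply a test or a date?**

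- 6.4 names the 7-month visit and telephone contact. The 7-month visit has 2 mL for HAI only, so it does not close the gap.
- 5.3 adds safety assessments without dates or content. The scheduled blood it mentions is for immunogenicity.
- 6.2 and 6.5 keep H1N1-infected subjects on the schedule. This could be read as wanting the STEP II Day 10 bloods, but without Dose #2 that visit has no date and no substitute is given.
- The STEP II laboratory entry criterion (4.32) covers platelets and ANC only. The Day 21 CBC is not a liver or renal test.
- Appendix IB is an exception for pregnancy deferrals: "Chemistries (SGOT, SGPT and creatinine ONLY) should be obtained prior to administration of Dose #2". Its entry total, 2 + 20 + 2 = 24 mL, includes the tube. These women are deferred, not permanently excluded, and their test is also tied to the Dose #2 visit.

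Count of scheduled post-Dose #1 chemistries for a permanently excluded subject under Appendix IA: 0.

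**Step 3. How far could this move the primary result?** Section 8.611 reports the proportion of all subjects with a Grade 3 or 4 event. With the planned 140 enrolled, each missed subject-level event moves it by 1/140 = 0.7 percentage points. In an age stratum of 40, the stated minimum, the shift is 1/40 = 2.5 points. For comparison, the exact 90% interval in Table 1 around an observed 5% is 2% to 10% with 120 subjects and 1% to 15% with 40. A subject excluded for a Grade 3 or 4 event under 4.45-4.48 already counts, so a missed laboratory event adds nothing there.

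**Step 4. Blood volume after the fix.** STEP I Day 21: 14-23 + 2 = 16-25 mL, below the 20-29 mL at screening.

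**The case against.** The strongest reply is that the sponsor chose one test after the full series of a licensed vaccine. Under Appendix IA no subject has chemistries between the doses. A Day 21 test in a few one-dose subjects would have no within-study comparator, and at 21-28 days after a dose it could miss a rise that a test at 7-13 days would catch. Both limits stand. They are reasons to list the results separately, not to leave these subjects untested. Footnote 8 gives vaccine toxicity as the purpose of the test, and the schedule ranks chemistries second, after HAI serum, when blood is short.

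The subjects of most concern are also the best covered clinically. Section 6.2 asks those with possibly vaccine-associated Grade 3 or 4 events to attend within 72 hours, where tests may be ordered on judgment. Serious events are followed to a final or stable outcome (7.1), and a vaccine-related one pauses enrollment and vaccination (8.5). A reader might infer that subjects stopped under 4.46 go unexamined; the documents do not support that. This narrows the gap to abnormalities without symptoms.

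A reader might also infer that 5.3 and 6.4 contradict each other. They can be read together: 5.3 refers to 6.4, and 6.4 does not cancel other visits. Neither names chemistries, and that is the part that matters here.

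**Conclusion.** The concern holds. Followed as written, the plan leaves a subject permanently excluded from Dose #2 with no scheduled liver or renal test at any time after Dose #1. The only qualification is the undated instruction for H1N1-infected subjects.

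The effect is modest. The documents do not say how many subjects will receive one dose only; I assume few. It is tempting to take 140 - 120 = 20 as a ceiling, but that is the planned allowance for non-evaluable subjects. A late Dose #2 or an out-of-window HAI sample also makes a subject non-evaluable, and those subjects can still have their STEP II Day 10 chemistries. Nor do the documents give a rate of liver or renal abnormality for this vaccine, so a probability of detecting one in these subjects cannot be supported.

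A reader might infer that the primary safety result is compromised. It is not. The shift is 0.7 points per missed event in 140, and nothing for subjects already counted with a Grade 3 or 4 event. The real loss is detection of symptom-free toxicity in one-dose subjects, together with unreported missing laboratory data among those excluded for reasons such as steroids, blood products or refusal. Subjects who withdraw consent are outside the point. The change is worth making because it is cheap and completes a check that the protocol already calls for.

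**What to change.** Add to Appendix IA footnote 8 and to section 6.4: *Subjects permanently excluded from Dose #2 who remain on study have SGOT, SGPT and creatinine drawn at the STEP I Day 21 visit, or at the visit where Dose #2 is ruled out if that is later.*

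Add to section 8.611: *The number of vaccinated subjects with no post-vaccine chemistry will be reported. Chemistry results after one dose will be listed separately from those at STEP II Day 10.*

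The cost is a few sentences and 2 mL more blood in a few subjects, usually at an existing draw and occasionally as one added draw. Appendix IB already draws the same chemistries between the doses in pregnancy deferrals, so the procedure is not new to sites. The drawback is timing: a result 21-28 days after one dose may miss a transient early rise and cannot be pooled with results 7-13 days after the second dose.

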**NOTE:**

For insufficient blood draws, priorities are as follows:

1. Serum for HAI for shipping to the University of Colorado, IMPAACT Immunology Laboratory
2. Toxicity labs (Chemistries)
3. CD4/CD8/CD19
4. PBMC's and plasma for shipping to the University of Colorado, IMPAACT Immunology Laboratory

## APPENDIX IB

### STEP II-SCHEDULE OF EVALUATIONS FOR WOMEN WHO BECOME PREGNANT BETWEEN DOSE #1 and DOSE #2 of STUDY VACCINE AND THEIR INFANTS

|                                                                  | STEP II                                            |                                       |                                        |                    |                                    |                                                  |
|------------------------------------------------------------------|----------------------------------------------------|---------------------------------------|----------------------------------------|--------------------|------------------------------------|--------------------------------------------------|
|                                                                  | Day 0
Entry
DOSE #2                          | Day 2
Post
2 nd Dose | Day 10
Post
2 nd Dose | Post
Delivery   | Unscheduled
visit  | Early Treatment
Discontinuation  |
|                                                                  | ≥14 weeks
gestation but
prior to
delivery | ±1 day                                | ± 3 days                               | Birth + 28
days |                                    |                                                  |
| MATERNAL EVALUATIONS                                      |                                                    |                                       |                                        |                    |                                    |                                                  |
| History                                              | X                                                  |                                       | X                                      | X                  | X                                  | X                                                |
| Physical exam                                        | X                                                  |                                       | X                                      | X                  | X                                  | X                                                |
| Neurological exam                                    | X                                                  |                                       | X                                      | X                  | X                                  | X                                                |
| H1N1 Vaccination                                     | X                                                  |                                       |                                        |                    |                                    |                                                  |
| Fetal Heart Rate                                                 | X                                                  |                                       |                                        |                    |                                    |                                                  |
| Follow up subject contact                            |                                                    | X                                     |                                        |                    |                                    |                                                  |
| Reactogenicity assessment and
interview           | X                                                  | X                                     | X                                      |                    | X                                  | X                                                |
| Respiratory specimen                                 |                                                    |                                       |                                        |                    | X                                  |                                                  |
| Chemistries                                          | 2 ml                                               |                                       | 2ml                                    |                    |                                    |                                                  |
| Complete blood count                                 | X                                                  |                                       |                                        |                    |                                    |                                                  |
| PBMC & plasma for CMI &
neutralizing antibodies  | 20 ml                                              |                                       | 20 ml                                  |                    |                                    | 20ml                                             |
| Serum for HAI                                       | 2 ml                                               |                                       | 2ml                                    |                    |                                    | 2ml                                              |
| TOTAL BLOOD VOLUMES                                       | 24 ml                                       |                                       | 24 ml                           |                    |                                    | 22 ml                                     |
| INFANT EVALUATIONS                                        |                                                    |                                       |                                        |                    |                                    |                                                  |
| History                                             |                                                    |                                       |                                        | X                  |                                    |                                                  |
| Physical exam                                       |                                                    |                                       |                                        | X                  |                                    |                                                  |
| Neurological exam                                   |                                                    |                                       |                                        | X                  |                                    |                                                  |

